#### Part 5: Step Activity Monitoring

Specific Aim 3 will be addressed with Part 5 of this protocol. After completion of Part 2-4, subjects will receive all three prosthetic limbs for use for a period of 30 days. All three limbs will be fitted with a Modus Health step activity monitor (SAM), which is a research-grade instrument for long-term assessment of ambulatory activity during day-to-day life. Subjects will also use an activity log to document their daily activities to allow for correlation between prosthesis used and activity. Subjects are free to use each prosthesis as they chose. Subject prosthetic preference will be based upon total activity time for each prosthesis.

#### SA3 Data Analysis:

Daily step counts and level of activity (low, medium, high) will be collected from each SAM attached to each prosthesis, and daily activity logs will be analyzed to determine which devices were used for specific activities (i.e. everyday use, leisure, housework). Together, this will help determine rationale for patient preference of prosthesis. Additionally these findings will be correlated with previous outcome measures from Parts 2-4.

#### Development of Prediction Model:

In order to develop guidelines for prosthetic prescription of ankle-foot devices, the goal of this proposal is to determine which factors and outcomes are most predictive of optimal performance to meet patient goals. To do this, initial analyses will consist of bivariate cross-tabulations, conducted using chi square analyses, based on clinical hypotheses between each potential explanatory variable. Variable selection for the multivariate model will be informed by bivariate findings. Logistic regression will then be performed with patient preference of prosthesis regressed on each of several domains (i.e. functional levels/outcomes, Activity levels, biomechanical parameters, among others). The models will control for multiple variables simultaneously. The C-statistic corresponding to the area under the receiver operating characteristic (ROC) curve will be used to assess overall predictive value. Theory-driven domain specific models (based on bivariate findings) and one parsimonious stepwise logistic regression model combining the domains will be created. This will help determine whether each distinct component predicts optimal prosthetic prescription outcome. Each domain-specific model will be adjusted for and controlled for confounding factors. The individual variables expressing the components of each domain will be entered as fixed predictors. Finally, a stepwise multiple regression will be applied to identify the set of clinical factors that represent the strongest independent predictors. The stepwise regression will be conducted through a series of domain-specific forward-regression models and one backward regression. The variables significant in these forward selection models will be placed in the backward model and will be removed at  $P = .10$ . The significant variables from the backward regression will be presented as the strongest independent predictive factors and be used to help guide prosthetic prescription.

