## **Outcome Measures**

The battery of functional outcome measures and surveys/guided interviews delivered after each acclimation period is delivered by a local researcher. Functional outcome measures include the 6-Min Walk, TUG, 4SST,

Amputee Mobility Predictor (AmpPRO), stair assessment index (SAI), and hill assessment index (HAI). Surveys/guided interview include Prosthetic Evaluation Questionnaire (PEQ), Short Form-12 (SF-12), and Orthotics and Prosthetics User Survey (OPUS).

- **6-Min Walk:** This test measures the distance an individual can walk in 6 minutes without help or encouragement. The 6-minute walk test is valid and reliable metric. It correlates with physical function and functional capacity (26, 27). This test has been proven to have good inter-rater and intra-rater reliability in transtibial amputees (26).
- **TUG:** The TUG measures the time taken by an individual to stand up from a standard arm chair, walk a distance of 10 feet, turn, walk back to the chair, and sit down. The TUG is both reliable and valid in a population with unilateral transtibial and transfemoral amputation (28). Additionally, the TUG has also been used as a measure to determine risk of falling (29, 30). This measure has also shown to correlate well with other measures of physical functioning (31).
- **4SST:** The 4SST is a higher order complex task assessing dynamic balance (32, 33).
- **AmpPRO:** The AmpPRO is a 21-item instrument designed to measure basic prosthetic mobility of individuals with lower extremity amputation (34).
- **HAI:** The HAI is a rated qualitative scale on how an individual with lower limb amputation negotiates up and down an incline (35).
- **SAI:** The SAI is a rated qualitative scale for stair negotiation (35).
- **PEQ:** The PEQ is self-report visual analog scale-style questionnaire for persons with lower limb amputations who use a prosthesis. It is used to evaluate the prosthesis and life with the prosthesis. It consists of 82 items with nine functional domain scales including ambulation, residual limb health, utility, appearance, sounds, frustration, perceived response, social burden and well-being. The PEQ also contains items beyond the subscales including satisfaction, pain, transfers, prosthetic care, self-efficacy, and importance (36).
  - **PEQ-Addendum:** This is an addendum to the PEQ, and it is a self-reporting measure to assess any stumbles and/or falls that occur during study protocol participation.

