#### Power Analysis:

| Site                                                | n   | n for subset |
|-----------------------------------------------------|------------|---------------------|
| VA New York Harbor Healthcare System (NYC)          | 30         | 15                  |
| Walter Reed National Military Medical Center (D.C.) | 30         | 15                  |
| VA Puget Sound Healthcare System (Seattle)          | 30         | 0                   |
| James J. Peters VA Medical Center (Tampa)           | 30         | 0                   |
| TOTAL                                        | 120 | 30           |

Figure 7. Total Subjects per site to be seen over the course of 3 year period

#### Specific Aim 1

Functional measures will be analyzed by multilevel (site) repeated measures analysis of variance. Because order of prosthesis will be randomized, there should be no order effect. However, order will be included in the initial analysis to test this assumption. Assuming an alpha error rate of 5% and within-group standard deviation of 5, 120 subjects will provide over 98% power to detect a 3 unit difference between at least two of the ESR groups for each of the functional measures.

### Specific Aim 2

Kinematic and kinetic measures will be analyzed by multilevel (site) repeated measures analysis of variance. Because order of prosthesis will be randomized, there should be no order effect. However, order will be included in the initial analysis to test this assumption. Assuming an alpha error rate of 5% and within-group standard deviation of 10, 30 subjects will provide 72% power to detect a 6-unit difference between at least two of the ESR groups for each of the measures.

### Specific Aim 3

This analysis will be performed using paired t-test to determine correlations between prosthesis chosen as per SAM data and which functional outcome measures are indicative of that choice. Additionally pair t-test will be performed between kinematic and kinetic data to again correlate with the prosthetic choice of the subject as demonstrated through the SAM data. Finally all SAM data will be evaluated against the activity journal to determine the roll of a specific activity goal and a specific prosthesis.

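### The prescription model screens mostly continuous and ordinal candidates with chi-square tables, which makes moderate real predictors easier to miss and conflicts with the paired t-tests named for Aim 3

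*Protocol*

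**What the plan says.** The Protocol section Development of Prediction Model sets out a sequence. First, "initial analyses will consist of bivariate cross-tabulations, conducted using chi square analyses, based on clinical hypotheses between each potential explanatory variable". Next, "Variable selection for the multivariate model will be informed by bivariate findings". Then "Logistic regression will then be performed with patient preference of prosthesis regressed on each of several domains", the domains being functional outcomes, activity levels, biomechanical parameters and others. Forward selection within each domain follows, and then one backward model with removal at P = .10. Chi-square is the only bivariate test that this section names.

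The outcome is a choice among three foot categories. Under Part 5: Step Activity Monitoring, "Subject prosthetic preference will be based upon total activity time for each prosthesis".

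The candidates are described elsewhere:
- **Functional tests (Outcome Measures):** for the 6-minute walk, "This test measures the distance an individual can walk in 6 minutes without help or encouragement"; for the TUG, "The TUG measures the time taken by an individual to stand up from a standard arm chair". The PEQ uses visual analog scales.
- **SAI and HAI:** the Aim 1 analysis text itself treats these as ordinal.
- **Step activity (SA3 Data Analysis):** daily step counts, plus a low/medium/high activity level and logged activity types.
- **Biomechanics (SA2 Statistical Analysis):** peak angles, moments and powers, in the 30-subject subset.
- **Demographics (Part 1a):** age, height, weight, time as a prosthesis user and injury etiology.

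Under Power Analysis, the Specific Aim 3 paragraph relates the chosen prosthesis to the functional measures, and then to the kinematic and kinetic data, by paired t-tests.

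**The concern.** A cross-tabulation can take a distance, a time or a joint moment only once it has been cut into classes. Cutting discards the information within each class, and Pearson chi-square then discards the order of the classes as well. The logistic models in the next step accept the same variables on their full scale, so the cut gains nothing, and the protocol cites no clinical threshold that would require one.

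The stake is the study's declared end point. The variables that survive selection are to be presented as the strongest predictors and used to guide prescription. A candidate given little weight at the screen may never reach the forward and backward steps.

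The protocol also gives two different bivariate methods for one question, chi-square in one section and paired t-tests in another, and neither suits a continuous score compared across groups of subjects.

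**Working it through.** **The plan's own figure.** No power, alpha or effect size is given for this screen, so there is nothing to reproduce for it directly. The nearest figure is for Aim 1: "within-group standard deviation of 5, 120 subjects will provide over 98% power to detect a 3 unit difference". With zero within-subject correlation, the SD of a paired difference is 5 × √2 = 7.07, and 3 ÷ (7.07/√120) = 4.65. Power is then Φ(4.65 − 1.96) = Φ(2.69) ≈ 99.6% for one pair, 98.6% with a Bonferroni adjustment, and 99.0% for the repeated-measures ANOVA with the third foot midway. The figure is consistent, but it concerns feet compared within subjects. The screen compares subjects grouped by preferred foot.

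**Inputs for the check.** From the protocol: n = 120, and 3/5 = 0.6 SD as a moderate difference, borrowed from Aim 1. Assumed, because the protocol gives none: the preference splits, the 5% screening level, the median or tertile cuts, normal scores, and preferred foot as the other variable in each table.

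**By formula, two preference groups of 40 and 80.**
- Full scale: λ = d × √(n1 × n2 / N) = 0.6 × √(40 × 80 / 120) = 0.6 × 5.16 = 3.10. Power ≈ Φ(3.10 − 1.96) = Φ(1.14) ≈ 87%.
- Median cut: this keeps 2/π ≈ 64% of the information, so λ = 3.10 × √0.637 = 2.47. Power ≈ Φ(2.47 − 1.96) = Φ(0.51) ≈ 70%.

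Simulation with expected shares of 1/3 and 2/3 gives 86% on the full scale, against 69% with median or tertile cuts.

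**By simulation, other splits of 120.** The full-scale test is the one-way F-test, standing in for the univariable logistic or multinomial test. Group means are in units with SD 5.

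| Split; means | Full scale | Median χ² | Tertile χ² | Loss (points) |
|---|---|---|---|---|
| 60/60; 0, 3 | 90% | 73% | 75% | 17, 15 |
| 40/40/40; 0, 0, 3 | 80% | 59% | 58% | 21, 22 |
| 40/40/40; 0, 1.5, 3 | 64% | 45% | 44% | 19, 20 |
| 60/40/20; 0, 0, 3 | 57% | 42% | 34% | 15, 23 |
| 72/36/12; 0, 1.5, 3 | 47% | 35% | 28% | 12, 19 |
| 72/36/12; 0, 0, 3 | 39% | 29% | 21% | 10, 18 |
| no difference | 4.9% | 4.8% | 5.6% | none |

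Over repeated runs and further splits the loss was roughly 10 to 24 points. Kruskal-Wallis loses only 1 to 3 points against the F-test, so the loss comes from the cutting and not from the normality assumption.

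**Sensitivity.**
- A 10% screen (two groups 1/3 and 2/3, 0.6 SD): 92% against 79% and 78%, a loss of 13 to 14 points.
- A strong predictor (0.8 SD, same two groups): 98% against 90% and 91%, a loss of 7 to 8 points.
- Three equal groups whose extremes are 0.8 SD apart: 88% against 70% and 69%. The relief for strong predictors therefore comes mainly once full-scale power is near its ceiling.
- The 30-subject subset (two equal groups, 0.6 SD): 36% against 23% and 19%. Power there is low under any test.

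**The paired t-test.** It compares two measurements on the same subjects. Whether those who prefer one foot differ from those who prefer another is a comparison between separate groups, which a paired test cannot make.

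**The case against.** **The screen is not a gate.** This is the strongest objection, and it stands. The text says "Variable selection for the multivariate model will be informed by bivariate findings", with no threshold and no exclusion rule; it also ties the tables to clinical hypotheses and calls the domain models theory-driven. A reader might infer that real predictors will be lost before modelling. The text supports a higher risk of that, not certainty.

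**The outcome is not named.** The sentence about cross-tabulations does not say what each variable is tabulated against. Preferred foot is the likely reading, because it is the outcome of the models that follow, but it is an inference.

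**Some candidates are truly categorical.** Etiology, low/medium/high activity level, logged activity type, and whether a subject commonly negotiates ramps or hills (Hypothesis 3.1) all suit a cross-tabulation. This limits the point to the remaining candidates, which are the majority.

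**Other full-scale analyses are mentioned.** SA3 Data Analysis speaks of correlating activity findings with earlier outcomes, and the Aim 3 paragraph names paired t-tests. The latter could compare chosen and unchosen feet within a subject, but that is a different question. They do not repair the screen, and they leave two sections to reconcile.

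**Cut points may be in an SAP.** That is fair, so their absence is not counted here. A reader might also infer that data-driven cuts would add false positives to the prescribing criteria. Nothing in the protocol says the cuts will be data-driven, and with the fixed-quantile cuts simulated the false-positive rate stays near 5%.

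**Conclusion.** The point holds in limited form. The stated screening test does not suit most of its candidates. At n = 120 with a 0.6 SD difference and a 5% screen, the chance of flagging a real predictor falls by roughly 10 to 24 points with median or tertile cuts. A more lenient screen narrows the loss, and strong predictors generally lose less.

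The size rests on assumed preference splits, assumed cuts and screening level, and an effect size borrowed from a within-subject contrast, so it shows the order of the loss and does not forecast it. The mismatch between test and variable type, and the conflict with the Aim 3 paragraph, depend on none of these assumptions. The change is worth making because the selected variables are meant to guide prescription.

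**What to change.** In Development of Prediction Model:
- Restrict chi-square cross-tabulations to truly categorical candidates, such as etiology, site, activity level and logged activity type.
- Assess continuous and ordinal candidates against preferred foot on their original scale, using univariable logistic likelihood-ratio tests (multinomial when all three feet are kept), with a transformation for skewed times and counts where needed.

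In the Specific Aim 3 paragraph of Power Analysis, replace the paired t-tests with the same method, so that the two sections agree.

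The cost is a wording change, with no new data, visits or subjects. The small downside is that effects are reported per unit and not as simple two-way tables, which can still be shown as description.

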## **Specific Aim 2:**

Specific Aim 2 will be addressed through a subset of  $n=30$  subjects which will undergo kinematic and kinetic biomechanical evaluations at the completion of each acclimation period for Parts 2-4. This will include kinetic and kinematic evaluation on level ground walking, and additional kinematic evaluation on inclines and declines.

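### Aim 3 assigns paired t-tests to a question of association with prosthesis choice, and its stepwise prediction model would present noise variables as prescribing factors with an inflated C-statistic

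*Protocol*

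**What the plan says.** In the Protocol, Part 5 (Step Activity Monitoring) gives each subject all three prostheses for 30 days and defines the outcome: "Subject prosthetic preference will be based upon total activity time for each prosthesis".

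Two sections then say how that choice is analysed.

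- **Power Analysis, Specific Aim 3:** "This analysis will be performed using paired t-test to determine correlations between prosthesis chosen as per SAM data", with functional outcome measures on the other side. It continues: "Additionally pair t-test will be performed between kinematic and kinetic data to again correlate with the prosthetic choice of the subject". No power or precision figure is given.
- **Development of Prediction Model:** "Logistic regression will then be performed with patient preference of prosthesis regressed on each of several domains", with functional, activity and biomechanical domains among those named. Bivariate results inform which variables go forward. Forward selection runs within each domain, and the variables that pass enter one backward model with removal at P = .10. The C-statistic assesses predictive value. A single model spans the domains ("one parsimonious stepwise logistic regression model combining the domains will be created"), and "The significant variables from the backward regression will be presented as the strongest independent predictive factors", to help guide prescribing.

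The biomechanical domain comes from Specific Aim 2, where it is a subset of 30 "subjects which will undergo kinematic and kinetic biomechanical evaluations at the completion of each acclimation period". The site table in Power Analysis places 15 of these at New York, 15 at Walter Reed and none at the other two sites.

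**The concern.** The protocol describes its end point as findings from which prescribing guidelines or algorithms can be built, and Aim 3 is the analysis meant to supply them. Three features put that at risk.

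1. The test named for Aim 3 in Power Analysis does not answer the Aim 3 question, and another section gives a different method for it.
2. The selection rule is data-driven at every stage. Its survivors are labelled as the strongest independent predictors, whether or not anything truly predicts choice.
3. One of the domains to be combined exists for a quarter of the subjects, at two of four sites. The plan does not say how the other 90 are handled.

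The stake is a set of prescribing criteria that looks discriminating in this sample and does not carry over to new patients.

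**Working it through.** **Plan's own figure.** Aim 3 has no stated power, precision or C-statistic, so there is nothing to reproduce.

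**Paired t-test.** The statistic is t = d̄ / (s_d / √n), where d_i is the difference between two measurements of the same quantity on subject i. It tests whether the mean difference is zero. The three-way choice appears nowhere in it, unless the pair is defined as the chosen foot against another foot. Even then it gives a mean difference, not a correlation.

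**Overlap of domains.** From the site table, 15 + 15 + 0 + 0 = 30, and 30/120 = 25%. A complete-case model that contains any biomechanical variable uses at most 30 subjects.

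**Candidate count.** The protocol gives none. As a guide, the Outcome Measures section lists six performance tests and nine PEQ domain scales. Counting SF-12 and OPUS once each gives 6 + 9 + 1 + 1 = 17 per foot, before any biomechanical variable. A range of 15 to 40 is therefore assumed.

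**Closed-form check.** With k independent noise candidates and entry level α, the chance that at least one passes is 1 − (1 − α)^k:

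| k | α = .05 | α = .10 |
|---|---|---|
| 15 | 0.54 | – |
| 20 | 0.64 | 0.88 |
| 30 | 0.79 | – |
| 40 | 0.87 | 0.985 |

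**Simulation of the selection rule.** All predictors were independent noise. Forward selection ran within each domain (likelihood-ratio p < .05, assumed because the protocol states no entry level), followed by pooled backward removal at .10. Preference was taken as one foot against the rest, at prevalence 1/3 or 1/2. There were 150 runs per setting, and a run that selected nothing counted as C = 0.50. Ranges are over the two prevalences:

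| n | Candidates | Runs keeping ≥ 1 predictor | Mean apparent C | 95th percentile | C in 2,000 new subjects |
|---|---|---|---|---|---|
| 120 | 15 | 52–55% | 0.58–0.59 | 0.71 | 0.50 |
| 120 | 20 | 66–75% | 0.60–0.62 | 0.71–0.74 | 0.50 |
| 120 | 30 | 78–81% | 0.63 | 0.74–0.76 | 0.50 |
| 30 | 15 | 59–63% | 0.67 | 0.87–0.93 | 0.50 |
| 30 | 30 | 84–86% | 0.79–0.80 | 1.00 | 0.50 |

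**Wider assumptions.** Further runs used 20 to 40 candidates in four domains, with entry at .05 to .10:

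- n = 120: 54–98% of runs kept a predictor, and mean apparent C was 0.58–0.71.
- n = 30: 52–99% of runs kept a predictor, and mean apparent C was 0.66–0.90.

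Mean inflation over the true 0.50 is therefore about 0.08 to 0.21 at n = 120 and 0.16 to 0.40 at n = 30.

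**The case against.** Several stronger readings are tempting, and the protocol does not support them.

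- **The combined model must shrink to 30 subjects.** It need not. Forward selection runs by domain first, and only variables that pass enter the backward model. If no biomechanical variable passes, all 120 can be used. No section prescribes complete-case analysis. When the biomechanical forward step was simulated on 30 subjects and the others on 120 (noise only, four domains, 200 runs), the final model fell to 30 in about 21% of runs (20 candidates, entry .05) to 72% (40 candidates, entry .10). Mean apparent C was 0.62–0.80. A figure of about 10 subjects per preferred foot would also need an even split, which the protocol does not give.
- **The C-statistic is stated to be in-sample.** It is not. That is inferred because no other data are named. The statistical analysis plan was not available, and it could add resampling.
- **Logistic regression is wrong for three categories.** The term can cover multinomial or one-versus-rest models, and Hypotheses 3.1 and 3.2 suggest two-way contrasts. The form is unclear rather than wrong.
- **The second t-test subtracts angles from moments.** The sentence literally reads that way, but loose drafting is more likely. Every subject is measured on all three feet, so comparing one measure on the chosen foot with the same measure on another foot would be legitimate. The text does not say that this is what is meant.

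The size also depends on an unstated candidate count. The protocol's appeal to clinical hypotheses and theory-driven models could shorten the list, and correlated candidates would lower the effective number.

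What stands is what the protocol itself fixes: a t-test assigned to estimate correlations, the selection rule, and the label given to its survivors. Later resampling could correct the C-statistic but would not change these three.

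**Conclusion.** The point holds as wrong as written, within limits. The paired t-tests cannot estimate the association that Aim 3 asks about, and they sit beside a regression given for the same purpose. The stepwise rule, applied to predictors with no information, keeps at least one in about half to nearly all runs. Mean apparent C is then about 0.58–0.71 at n = 120 and 0.66–0.90 at n = 30, where the truth is 0.50. These figures assume 15 to 40 independent candidates, entry at .05 to .10, one foot against the rest, no dropout, and a C-statistic computed on the fitting data. The n = 30 figures apply only if a biomechanical variable enters a complete-case combined model.

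A reader might infer that the resulting prescribing criteria will be spurious. The simulations show what happens when nothing predicts choice. They do not show that nothing does. Over-optimism is the firm conclusion, and spurious factors are a high probability if true signals are weak.

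Because this analysis is meant to feed prescribing guidance, it should be corrected before the data are analysed. No data collection, randomisation, or Aim 1 or Aim 2 comparison is affected.

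**What to change.** 1. In Power Analysis, Specific Aim 3, replace the paired t-tests with the regression from Development of Prediction Model. Alternatively, restrict them to the same measure on the chosen versus another foot and label them descriptive.
2. State the form of the model for a three-category preference, for example multinomial or named one-versus-rest contrasts.
3. Keep biomechanical variables out of the combined n = 120 model. Report them as a separate exploratory n = 30 model; the domain-specific models already planned provide the place for it.
4. Replace bivariate screening with a short candidate list fixed in advance. At the least, repeat the whole selection process in a bootstrap and report the optimism-corrected C-statistic and selection frequencies as the headline result.
5. Describe surviving variables as candidate predictors that need validation.

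The cost is wording and programming, with no added subjects or visits. The downside is a lower reported C-statistic and fewer declared predictors.
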